### Randomization and treatment allocation

Participants are randomized to either the “Phase 1 GI” or “Phase 2 GI” treatment arm by REDCap electronic data capture tools hosted at University of California, San Francisco. REDCap is a secure, web-based software platform designed to support data capture for research studies (53, 54). We loaded REDCap with a randomization sequence generated in SAS software 9.4 (55) using block randomization with varied permutations, with equal allocation to treatment arm and balanced by gender, age group, and city of residence. Due to the nature of the intervention, blinding the participants and study staff is not possible. Study staff inform participants of group assignment during the enrollment appointment, following baseline survey completion. The investigators are blinded to allocation, as is the trial methodologist ([name]), who will run the final analyzes.

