### Measures

#### Exposure

The primary exposure is intervention arm assignment (see all measure in Table 1). Secondary exposure variables include: receipt of financial mentoring (yes/no) and participation in peer discussion groups (yes/no) during each 3-month study interval. Because engagement with any treatment option will vary by individual, we will also capture intervention dose (e.g., mentoring sessions attended) on study monitoring forms.

**Table 1 tab1:** Study measures: domains, instruments, and time points.

Domain	Instrument/measure	Data source and frequency
Primary exposure		
Intervention	Randomization arm (GI receipt in phase I or phase II)	Study records
Primary outcomes		
Financial well-being	Investments in future (Enrollment in education/training)	Quarterly surveys
Mental Health	CESDR-10: major or probable major depressive episode (64, 65)	Quarterly surveys
Unmet need for health services	Unmet need for mental health services	Quarterly surveys and monthly brief check-ins
	Unmet need for sexual and reproductive health services	Quarterly surveys and monthly brief check-ins
Secondary outcomes		
Financial well-being	Savings, Debt	Surveys at baseline, 6, 12, 18, 24 months
	Credit score	Assessed at baseline, 6, and 12 months
	Financial Capability (knowledge, skills, practices, mindset) (45)	Every six months: baseline, 6, 12, 18, 24 months
Mental health	Anxiety – moderate–severe: score ≥ 10 on GAD-7 (66, 67)	Quarterly surveys
	Hope/ future orientation (68, 69)	Surveys at baseline, 6, 12, 18, 24 months
Physical health	General health (70); fatigue	Surveys at baseline, 6, 12, 18, 24 months
Secondary exposure		
Intervention dose	Engagement with optional intervention components (peer groups and mentoring)	Study monitoring forms
Covariates/Mediators		
Demographics	Age, gender identity, housing/living situation, household membership, income, employment	Quarterly surveys
Strengths and assets	Resilience (71); self-esteem; Black identity (72); decision-making and goal-setting	Frequency varies – six-month and annual surveys
Social and structural contextual factors	Experienced discrimination (73); alcohol and substance use (74); social support (75, 76); social cohesion (77, 78); incarceration; relationship violence (79); trauma (80); prosocial involvement; food security	Frequency varies - quarterly; six-months; and annual surveys

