#### Primary analyses

Our primary analyses will test the hypothesis that GI will improve all primary outcomes at 12 months (H1). Specifically, we hypothesize that participants receiving GI in phase I will have (a) greater increases in investments in their future; (b) greater decreases in depressive symptoms, and (c) larger reductions in unmet need for MH and SRH services at 12 months than the no-GI arm.

We will use generalized estimating equations (GEE) to test our primary hypotheses and this analysis will follow an intent-to-treat approach by including all randomized participants. Our primary interest is to estimate the marginal or population-average effects of intervention participation on these primary outcomes rather than the effect for a hypothetical average subject (91). Moreover, within-subject outcome correlations are considered nuisance parameters rather than quantities of interest to be modeled explicitly. Accordingly, GEE can be used to estimate the marginal effects using difference-in-differences (DID) comparisons of post-baseline (follow-up) measurements of the Phase 1 GI group with the comparison arm in the main trial Phase. Since our primary outcomes are dichotomous, these models will employ a logit link and assume a binomial distribution. For each model, we will include indicators for study arm, time and the interaction between study arm and time to examine the relative change in outcomes for each arm during Phase 1. If changes in each outcome do not follow a linear trend, we will explore alternative relationships including polynomial and spline terms. Alpha (α) will be set at 0.05 for each of our planned comparisons. Any additional post-hoc comparisons (e.g., paired comparisons of groups at each time point) will maintain a nominal alpha of 0.05 through the use of simulation-based stepdown multiple comparison methods (92).

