Though GEE estimates are consistent even if the correlation structure is mis-specified, GEE’s statistical efficiency improves as the working correlation structure more closely approximates the actual correlation structure (93, 94): therefore, various correlation structures suitable for the study’s design will be considered (e.g., exchangeable; M-dependent) (94). The QIC statistic will be used to select the final correlation structure (95). Additional covariates, including baseline demographic characteristics, psycho-social covariates and social and structural contextual factors will be included if they improve QIC. Robust Huber-White “sandwich” standard errors will be used to obtain correct inferences even if the chosen correlation structure remains slightly misspecified. GEE case deletion diagnostics (e.g., DFBetas, Cook’s D) will be used to investigate whether influential cases are present; if so, results will be reported with and without influential cases included (96).

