#### Exploratory mediation and moderation analyses

We will conduct a number of exploratory mediation and moderation analyses. For example, in mediation analyses we will investigate whether covariates, such as food insecurity, or interim financial well-being outcomes, such as debt, credit, or income, measured at 3, 6, and 9 months mediate the relationship between intervention assignment and subsequent mental health outcomes (i.e., less anxiety and depressive symptoms) measured at 6, 9, and 12 months. We will also investigate whether changes in financial and mental health outcomes mediate the relationship between intervention assignment (GI) and reduced unmet service needs. Finally, we will explore whether intervention impacts are different by gender, parenting status, or living situation (moderation).

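### The QIC rule for covariates in the primary GEE permits, without saying it intends, adjustment for variables measured after randomisation

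*Protocol article*

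**What the plan says.** All of this is in the protocol article.

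- **Primary analyses, aim.** For the primary hypotheses, "this analysis will follow an intent-to-treat approach by including all randomized participants", and "Our primary interest is to estimate the marginal or population-average effects of intervention participation on these primary outcomes".
- **Primary analyses, model terms.** In a logistic GEE, "we will include indicators for study arm, time and the interaction between study arm and time".
- **Primary analyses, covariates.** QIC first selects the working correlation structure. The next sentence gives it a second task: "Additional covariates, including baseline demographic characteristics, psycho-social covariates and social and structural contextual factors will be included if they improve QIC".
- **Measures, Table 1.** Demographics, strengths and assets, and social and structural contextual factors share the heading "Covariates/Mediators". The contextual row includes food security, social support, substance use and incarceration, and its timing is given as "Frequency varies - quarterly; six-months; and annual surveys".
- **Secondary outcomes, last paragraph.** The covariates are described as possible confounders, effect modifiers or mediators.
- **Exploratory mediation and moderation analyses.** The question there concerns candidate mediators between assignment and later mental health: "whether covariates, such as food insecurity, or interim financial well-being outcomes, such as debt, credit, or income, measured at 3, 6, and 9 months".
- **Randomization and treatment allocation.** The sequence was generated "with equal allocation to treatment arm and balanced by gender, age group, and city of residence". No sentence fixes these three factors in the primary model.

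**The concern.** A randomised comparison estimates the total effect of assignment only if the model conditions on nothing that assignment can change. If GI reduces food insecurity, and food insecurity raises the risk of depression, a model holding current food insecurity fixed drops that route from the arm effect. What remains is not the intention-to-treat effect that the section sets out to estimate.

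QIC gives no protection. It scores how well the model predicts the outcome, and a follow-up mediator may predict it as well as a baseline prognostic factor does.

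There are two lesser consequences. Gender, age group and city, on which allocation was balanced, enter only if QIC accepts them. And because selection runs model by model, the four primary outcome measures in Table 1 can end up with different covariate sets, which makes their odds ratios harder to set side by side.

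**Working it through.** The plan gives no figure for covariate adjustment, so there is none to reproduce. The power statement does not bear on this point.

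**Step 1. Set the sections side by side.** The covariate sentence names three classes, and baseline stands before the first. The contextual class in that sentence has the same name as a row in Table 1. That row contains food security and is collected partly during follow-up. The mediation section takes food insecurity at 3, 6 and 9 months as a candidate mediator. So one variable belongs both to a class eligible for the primary model and to the list of possible mediators, and no sentence limits the primary model to its pre-randomisation value. Demographics are also collected quarterly, and for that class the sentence does state baseline.

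**Step 2. What conditioning removes.** Let m0 and m1 be the follow-up prevalence of food insecurity without and with GI, and r1 and r0 the risk of depression with and without food insecurity. With no interaction and no other common cause of the two:

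- total effect = direct effect + (m1 − m0) × (r1 − r0)
- effect with current food insecurity held fixed = direct effect

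The amount lost is (m1 − m0) × (r1 − r0). Assumed values, none from the document: r1 = 0.50, r0 = 0.25, m0 = 0.50, no direct effect.

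- Control risk: 0.50 × 0.50 + 0.50 × 0.25 = 0.375.
- If m1 = 0.30: 0.30 × 0.50 + 0.70 × 0.25 = 0.325. Total −5.0 points; adjusted 0.
- If m1 = 0.40: 0.40 × 0.50 + 0.60 × 0.25 = 0.350. Total −2.5 points; adjusted 0.
- If m1 = 0.50 (GI does not move food insecurity): nothing is lost.

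The zeros follow from assuming no direct effect. The example shows the mechanism and does not forecast the loss.

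**Step 3. Behaviour of the stated model and of QIC.** A logistic GEE (exchangeable correlation, robust standard errors) was simulated with 300 participants, 1:1, five visits, no attrition, 200 runs per scenario, and time coded as baseline versus follow-up. GI lowers the prevalence of a binary mediator from 50% to 25%. All mediator and effect strengths are assumptions. Entries are the mean arm-by-time log odds ratio and, in brackets, the share of runs with p < 0.05.

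| Scenario | No covariate | Baseline value | Follow-up value |
|---|---|---|---|
| Full mediation (mediator log-OR 2.0, no direct effect) | −0.37 (34%) | −0.38 (34%) | +0.01 (2.5%) |
| Part mediation (mediator log-OR 1.2, direct log-OR −0.35) | −0.50 (59%) | −0.50 (59%) | −0.27 (23%) |

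In the second scenario the loss is (0.50 − 0.27) / 0.50 = 46%. Adding the follow-up value improved QIC in 100% of runs in both scenarios. Adding the baseline value improved it in 100% and 99%. QIC would have admitted either, and only one of them changes what is being estimated.

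**The case against.** The strongest reply is that baseline opens the list and can be read over all three classes. The surrounding text gives some support. Preliminary analyses deals with arms that differ at baseline, the Discussion speaks of adjusting for baseline differences, and the 3-, 6- and 9-month measures appear only in a section marked exploratory. On that reading the bias is absent, as the baseline column above shows. This stands as a possible reading, so a reader should not infer that the plan intends to adjust for follow-up variables. But the sentence does not settle the matter, and the primary estimate should not depend on how an analyst parses it.

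It can also be said that Table 1 suits time-varying adjustment poorly, because strengths and assets are measured only six-monthly or annually. That is so at 3 and 9 months. The comprehensive annual survey nevertheless collects covariates at 12 months, the time point of the primary hypothesis.

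Three other points limit the concern:

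- The mediation section asks whether food insecurity mediates. It does not assert that it does.
- The methodologist who runs the final analyses is blinded to allocation. That limits steering of covariate choice towards a preferred arm effect, but it does not stop QIC from accepting a mediator.
- The section contrasts the marginal effect with one for a hypothetical average subject, which is the usual distinction between GEE and subject-specific models. A reader might infer that a covariate-adjusted GEE contradicts the stated aim and that a standardised risk difference is required. The text does not support that; such a summary is optional.

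Finally, an article may leave the covariate list to an analysis plan that is not shown. The point here is not a missing list but a selection rule that the article states.

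**Conclusion.** The point holds as a defect of wording with consequences for the primary analysis. The rule permits post-randomisation covariates in the intention-to-treat model and hands the choice to a criterion that cannot recognise them. This could remove part of the GI effect.

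The size is not determined by the document. It runs from nothing, if only baseline values are used or GI does not move the covariate, through about half in the part-mediation scenario, to the whole effect if everything passes through the included variable. The last two rest on assumed strengths. It would go too far to say that the primary model will adjust the effect away.

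Leaving gender, age group and city optional is a lesser matter, mainly of efficiency. So is the freedom for covariate sets to differ between primary outcomes, which mainly affects comparability. The same rewording cures both.

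**What to change.** Replace the covariate sentence in Primary analyses with wording to this effect: each primary model includes gender, age group and city of residence, plus any further covariates named in advance and measured before randomisation; no post-baseline covariate enters a primary model; QIC is used only to choose the working correlation structure. State that follow-up psychosocial, contextual and financial measures are kept for the exploratory mediation analyses. If a separate analysis plan already contains this limit, bring the two texts into line. A standardised risk difference alongside the odds ratio may be added but is not needed to resolve the point.

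The cost is one paragraph, settled before the outcome analysis, and no new data: the balancing factors are already known, and the baseline survey is completed before participants learn their assignment. What is given up is some data-driven flexibility, including the chance to pick up a strong baseline predictor that nobody named in advance.

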#### Sample size estimation

Power analyzes were generated using the equation defined by Diggle et al. (97) to compute minimum detectable effect sizes for the primary analyses to address Hypotheses 1a-1c. The study will begin with 300 participants equally allocated to two study groups. Assuming 25% attrition over 12 months, we anticipate an average of 4.3 observations from 300 participants will be available for analysis of investments in the future and mental health outcomes and an average of 5.7 observations for analysis of unmet service need outcomes. Assuming *α* = 0.05 and power = 0.80, with four highly correlated post-baseline measurements [intraclass correlation (ICC) = 0.20–0.80] and a range of outcomes for waitlist control participants (change in each outcome between 5 and 40%), we will have sufficient power to detect differences as low as 5.7–10.7% for increase in enrollment in educational or training programs and decrease in depression, and 4.5–10.6% for decrease in unmet service need, respectively, in the intervention arm compared to waitlist controls.

#### Secondary analyses

We will determine if BEA receiving GI in Phase 1 who opt-in to peer discussion groups and financial mentoring will have larger increases in odds of investment in the future, larger declines in odds of depressive symptoms and larger declines in odds of unmet mental and sexual health service needs at 12 months compared to those who did not opt into these support programs (H2). We will use the same modeling approach as described above for H1 used to test H2 except that analysis will be restricted to a single arm of the study (those receiving GI in phase I or those receiving GI in phase II).

As in our preliminary analyses, we will employ causal inference methods to adjust for any differences between sub-strata [e.g., individuals who do or do not opt in to financial mentoring or peer discussion groups at baseline or due to differential loss to follow-up]. As in our primary analyses, we will use logistic GEE to model our dichotomous outcomes, and continuous GEE specifications for continuous measures. We will test H2 via DID comparison of post-baseline measurements in the Phase 1 GI group during Phase 1 (as in H1). All comparisons for secondary analyses (H2 through H4) will be tested at *α* = 0.05 per comparison.

We will test (H3)–BEA receiving GI in Phase 1 will not experience a significant decline in odds of enrollment in educational or training programs, a significant increase in odds of depression or a significant increase in odds of unmet mental and sexual health service needs following removal of the GI (between month 12 and 24)–using an interrupted time series (ITS) approach. For these ITS analyses, we will include indicators for phase, time and the interaction between phase and time to examine the slope in each outcome during Phase 1, the presence of an immediate change in each outcome after removal of GI (level effect), as well the change in slope for each outcome during Phase 2 (slope). If changes in outcomes do not follow a linear trend, we will explore alternative relationships including polynomial and spline terms.

Following completion of Phase 2, we will assess (H4)–whether participants who received GI in Phase 2 who enrolled in peer discussion groups and/or financial mentoring during Phase 1 will experience a larger increase in odds of investments in the future, larger declines in odds of depressive symptoms, and larger declines in odds of unmet MH and SRH service needs compared to participants who received GI in Phase 2 and did not enroll in the opt-in financial programming during Phase 1. Analyses for H4 will follow the same analytical approach as described in H2 except that this analysis will be restricted to participants receiving GI in Phase 2. We will test H4 via DID comparison of post-baseline measurements in the Phase 2 GI group during Phase 2 (as in H1).

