### Research hypotheses

Our primary research question is to understand the potential impacts of GI on BEAs investment in their future (education, employment, training), mental health (depressive symptoms), and unmet mental health (MH) and sexual/reproductive health (SRH) service needs. We are also interested in learning if complementary financial supports propel greater impact on health outcomes and understanding to what degree GI impacts dissipate after the transfers end. Thus, our hypotheses are as follows.

*H1*: *GI will improve all outcomes*. Youth receiving GI in phase I will have greater increases in investments in their future (H_1a_), greater decreases in depressive symptoms (H_1b_), and larger reductions in unmet need for MH and SRH services (H_1c_) at 12 months than those who do not received GI in phase I.

*H2*: *GI + financial supports will improve outcomes more than GI alone*. Participants receiving GI in phase I who participate in mentoring or peer discussion groups will have greater increases in investments in their future (H_1a_), greater decreases in depressive symptoms (H_1b_), and larger reductions in unmet need for MH and SRH services (H_1c_) at 12 months than those not opting into financial support programs.

*H3*: *Gains from GI will be sustained*. Participants receiving GI in phase I will not experience a decline in odds of enrollment in educational/training programs (H_3a_) or an increase in odds of depressive symptoms (H_3b_) or unmet need for MH and SRH services (H_3c_) following the removal of GI (between month 12 and 24).

*H4*: *Accessing complementary financial supports prior to receiving GI will improve overall outcomes.* Among BEA who do not receive GI in phase I, those who engage in mentoring or peer discussion groups in phase I will have greater increases in investments in their future (H_4a_), greater decreases in depressive symptoms (H_4b_), and larger reductions in unmet need for MH and SRH services (H_4c_) at 24 months than BEA who did not opt-in into the financial programming prior to receiving GI.

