## Discussion

The BEEM Project addresses the important impact of decades of structural racism and inequitable access to opportunity and wealth generation for BEA, while also addressing scientific knowledge gaps regarding the impacts of GI on financial well-being and health outcomes. The randomized controlled crossover design supports the ability to draw causal inferences while ensuring all participants have access to no-strings-attached cash payments. This study will illuminate the impacts of complementary financial capability programming (i.e., mentoring, peer discussion groups) and their ability to bolster the effects of GI as an accompanying policy program. The extended data collection period will aid understanding of sustained impacts of GI one-year after payments end, filling a critical gap in knowledge on the degree to which the impacts of GI dissipate (follow-up for most GI projects have rarely extended beyond a few months). Results about the extended impact of GI can also provide evidence about augmenting health trajectories over the life course.

Importantly, results of the study will also help determine the utility of GI as a strategy to tackle racial health disparities. The focus of our project is on empowering low-income BEA, a group that has been made vulnerable by a history of intersecting social, economic, and political systems that result in lasting economic inequities and denied opportunities. This study will provide evidence about targeting GI within a group whose financial vulnerability and health inequalities have been created by structural racism and impact health transitions to adulthood. We apply anti-racism praxis and actively engage with communities, an approach vital for informing our approaches to affirming the autonomy of BEA, allocating and distributing resources, and challenging institutional (including research) norms.

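### H3 reads the absence of a significant decline in one arm as maintained gains, with no margin, and its model terms do not measure change from month 12

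*Protocol article*

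**What the plan says.** Under Research hypotheses, H3 is titled "Gains from GI will be sustained". It predicts that the arm paid in Phase I "will not experience a decline in odds of enrollment in educational/training programs" between months 12 and 24, with parallel statements for depressive symptoms and unmet service need.

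Under Secondary analyses the hypothesis becomes "BEA receiving GI in Phase 1 will not experience a significant decline in odds of enrollment in educational or training programs", again with parallel statements for the other outcomes. The word *significant* is now part of the hypothesis. The method is an interrupted time series with terms for phase, time and their interaction, examining "the presence of an immediate change in each outcome after removal of GI (level effect), as well the change in slope". On the error rate: "All comparisons for secondary analyses (H2 through H4) will be tested at" alpha 0.05 per comparison.

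Under Sample size estimation, the equation was used "to compute minimum detectable effect sizes for the primary analyses to address Hypotheses 1a-1c". No power or precision is given for H3. Neither statement of H3 gives a margin, an equivalence bound or a confidence-interval rule, and neither makes H3 explicitly conditional on H1.

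**The concern.** A hypothesis of no change is paired with a test for a difference, so H3 is satisfied by failing to reject. Failure to reject can mean that the gain lasted, or that the data could not show its loss. Poorer retention or noisier measurement makes the second more likely, so the rule favours the hypothesis as data quality falls.

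The model terms are a second problem. The wording of H3 concerns decline after month 12. The level and slope-change terms compare Phase 2 with the continuation of the Phase 1 trend. These are different quantities when the outcome was still rising during Phase 1.

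Durability is one of the trial's advertised contributions. The Discussion describes the extended follow-up as "filling a critical gap in knowledge on the degree to which the impacts of GI dissipate".

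**Working it through.** **The plan's own figure.** None exists for H3. The H1 minimum detectable differences (5.7-10.7 points for enrollment and depression) serve here only as plausible sizes of a gain that could be lost. They were not reproduced exactly. The repeated-measures binary formula with 150 per arm, 4.3 observations and two-sided 0.05 gives 5.3 and 10.0 points at ICC 0.2, for increases from 5% and 40%. At ICC 0.8 it gives 8.6 and 14.8. The article's inputs are ambiguous, so this does not show the H1 figure to be wrong, and nothing below depends on it.

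**Inputs from the article.** 300 randomised 1:1, so 150 in the H3 arm. 25% attrition over 12 months leaves 150 × 0.75 = 112.5, about 112. ICC 0.20-0.80. Quarterly surveys, so nine time points from 0 to 24 months. Alpha 0.05.

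**Assumptions.** Two-sided test; month-12 prevalence 30% or 50%; attrition accruing evenly to month 12 and none after; exchangeable correlation; Phase 1 trend flat, so that the level or slope term equals the loss itself.

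**Power of the H3 model.** Logit model with intercept, time, phase, and phase × time since month 12. Var(β) = (Σ D′V⁻¹D)⁻¹ summed over participants; power ≈ Φ(|β|/SE − 1.96). An abrupt loss is tested with the level term and a gradual loss by month 24 with the slope-change term.

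- Example 1: 30% prevalence, abrupt 5.7-point loss, ICC 0.5. β = logit(0.243) − logit(0.300) = −0.289, SE 0.220, z = 1.31, power = Φ(−0.65) = 0.26.
- Example 2: 50% prevalence, gradual 10.7-point loss, ICC 0.5. β = logit(0.393) − logit(0.500) = −0.435, SE 0.290, z = 1.50, power = Φ(−0.46) = 0.32.

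| Complete loss of | Pattern | ICC 0.2 | ICC 0.5 | ICC 0.8 |
|---|---|---|---|---|
| 5.7 points | abrupt | 16-18% | 22-26% | 47-54% |
| 5.7 points | gradual | 10-11% | 12-15% | 24-29% |
| 10.7 points | abrupt | 42-50% | 60-70% | 94-97% |
| 10.7 points | gradual | 22-28% | 32-41% | 66-78% |

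At ICC 0.5, loss of 5.7 points is non-significant in 100 − 26 = 74% to 100 − 12 = 88% of trials. Loss of 10.7 points is non-significant in 100 − 70 = 30% to 100 − 32 = 68%. Autoregressive correlation or further attrition in year 2 lowers power in most scenarios. Unmet need is also collected at monthly check-ins, which this calculation does not use.

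**The opposite error.** Suppose prevalence rises from 40% to 50.7% in Phase 1 and then stays flat, so nothing is lost. Phase 1 slope = logit(0.507) − logit(0.400) = 0.028 + 0.405 = 0.433 per year; Phase 2 slope = 0; slope change = −0.433. With SE 0.364, 0.289 and 0.183 at ICC 0.2, 0.5 and 0.8, this term is significantly negative 22%, 32% and 66% of the time.

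**Precision of the direct contrast.** For month 24 minus month 12 in 112 people, SE = √[2p(1 − p)(1 − ICC)/112].

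- Narrowest: p = 0.3, ICC 0.8 gives √(0.084/112) = 2.74 points, 95% half-width 5.4.
- Widest: p = 0.5, ICC 0.2 gives √(0.40/112) = 5.98 points, half-width 11.7.

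The half-width is therefore about 5-12 points, comparable with the whole H1 detectable effect.

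**The case against.** The strongest reply is that the article's stated aim is graded. The Abstract and Research hypotheses speak of how far effects dissipate, and the time-series model yields level and slope estimates as well as a verdict. H3 is secondary. A condensed article may leave interpretation rules to an analysis plan.

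Much of this stands. It lowers the severity and rules out several stronger readings that a reader might infer:

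- *That a null result will be published as proof of durability or as a policy conclusion.* Nothing in the article says so.
- *That H3 is underpowered in every case.* No H3 power is stated. The table rests on assumed prevalence and attrition, and at ICC 0.8 an abrupt 10.7-point loss would seldom be missed.
- *That an outcome GI never improved will be reported as sustained.* The title of H3 presupposes a gain, and the Dissemination section reports H1 before H3. What is missing is an explicit condition.
- *That the rule errs only towards H3.* The plateau example shows that it can also err against it.

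The appeal to a separate analysis plan does not fully answer the point. The criterion of no significant decline is written into the hypothesis, so adding a margin would change the stated rule, not fill in a detail. The Discussion's limitations name time shocks as a threat to H3, but not the reading of a null result.

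**Conclusion.** The concern holds as a fault in the stated decision rule and should be fixed. Non-significance without a margin does not show maintenance at any level of power, and that conclusion needs no assumptions. Its practical size does. At ICC 0.5, under the assumptions listed, complete loss would go undetected about 74-88% of the time for a 5.7-point gain and 30-68% for a 10.7-point gain. The risk is small for an abrupt 10.7-point loss at ICC 0.8. Separately, the level and slope-change terms answer a different question from the one H3 asks. The randomised H1 comparison and the sample size are unaffected.

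**What to change.** 1. Reword H3 as estimation of the month-24 minus month-12 change in the Phase 1 GI arm, for each primary outcome, with its 95% CI. The contrast can be obtained from the same GEE model. Level and slope changes can be kept as description of the trajectory.
2. Use *sustained* only where H1 showed a gain for that outcome and the CI excludes a loss larger than an absolute margin. Set the margin per outcome before the Phase 2 data are analysed. A fraction of the observed month-12 difference would not serve, because that difference is itself estimated.
3. Otherwise report: no decline detected; losses up to X not excluded, with X taken from the CI limit.

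**Cost.** No new data are needed, only rewording and one margin per outcome. The price is that many H3 results will be inconclusive. With zero true change, n = 112 and one-sided 0.025, power is Φ(margin/SE − 1.96). Over prevalence 30-50% and ICC 0.2-0.8, an illustrative 5-point margin gives 13-45% power and would need 264-1,256 people in the arm for 80%. A 10-point margin gives 39-95% and would need 66-314. These margins are examples; the article supplies none.

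The change does not supply an untreated comparator for months 12-24, when the other arm receives GI, so the time-shock limitation should stay in the text.
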